## Laboratory Evaluations

### Clinical Laboratory Evaluations

The collection of blood and urine samples for analysis will be carried at the clinical site (Q-Pharm, Australia). Analyses for the biochemical hematological results including the serum pregnancy test and the microscopic urine analysis (if required) will be performed at a nominated pathology laboratory. Tests performed at Q-Pharm include, urinalysis, urine pregnancy test, alcohol breath test, urine drug test and rapid antigen test for group A streptococci. It will be performed with QuickVue In-Line Strep A test which is currently not licensed in Australia, however it is licensed and widely used in US. These tests will be imported from US for the purpose of use in this trial only. The test will be used as per manufacturer’s instructions. Laboratory evaluation will be undertaken for all participants at screening, prior to each immunization and at every scheduled clinic visit, (refer to Appendix D for the tests required and blood volume for different samples). The samples required include:

• Blood sample for hematology, serum biochemistry and serology including ASOT and α-DNAse B (please refer to Appendix D for samples types, volumes and tests that will be undertaken at different time point including the laboratories that will perform the tests)

• Urine sample for dipstick urinalysis for all participants and for pregnancy test for female participants.

The laboratory parameters to be monitored are as follows:

• Hematology: full blood count (FBC) [hemoglobin (Hb), red blood count (RBC), hematocrit (Hct), mean cell volume (MCV), platelet count (Plts)], total white blood cell count (WBC) and differential,

• Serum/Biochemistry: Sodium, Potassium, Glucose, Bicarbonate, Chloride, Urea (Blood Urea Nitrogen; BUN), Creatinine, Calcium, Phosphorus, Creatinine Albumin, Total Bilirubin, At screening parameters to be measured will include: Creatine Phosphokinase (CPK), Sodium, Potassium, Bicarbonate, Chloride, Liver Function tests (LFTs: Alkaline Phosphatase, Alanine Aminotrasferase (ALT), Aspartate Aminotrasferase (AST)),

• Cardiac troponin T, C-reactive protein (CRP), C3 complement, Anti-streptolysin O Titer (ASOT) and α-DNAse B antibody levels, auto-antibody screen (ANA) and Anti-CCP antibody,

• A -HCG serum pregnancy test will be performed for all female participants at screening. Urine pregnancy tests will be performed prior to each dose. The results must be available and negative prior to each administration of study product.

• As part of the screening process, blood samples from the participants will be tested for antibodies for blood borne viral pathogens including Human Immunodeficiency virus, type 1 and type 2 (HIV-1/-2), Hepatitis C virus (HCV), Hepatitis B virus surface antigen (HBsAg).

• Urinalysis: urinalysis including protein, glucose and hemoglobin; Complete urinalysis to be performed with microscopic analysis if the dipstick urinalysis is abnormal (any blood or > trace protein).

• Urine Drug Test: At screening, and on pre vaccine administration (Day 0 and Day 56). The urine drug screen can detect the drugs such as Amphetamines, Methamphetamines, Barbiturates, Benzodiazepines, Cocaine, Methadone, Opiates, Phencyclidine, Tetrahydrocannabinols and Tricyclic antidepressants at the Q-Pharm clinic. If the result of the test is positive volunteers may be allowed to continue, or may be delayed or withdrawn according to site specific instructions. This will also include an alcohol breath test at screening, on Day 0 and day 56 prior to vaccine administration.

### Special Assays or Procedures

Serum samples will be required for evaluation of the serologic responses of the vaccine candidate, including ELISA and bactericidal abilities of the vaccine induced J8 specific antibodies as well as antibodies to diphtheria toxoid.

Sera samples will also be kept for each participant as indicated in this protocol and tested should better assay become available for detecting cross reactive antibodies that have been induced due to the vaccine candidate.

Samples of sera will be collected from the participants prior to each injection, at day 28 after each injection and at the scheduled clinic visits as indicated in this protocol. Immunogenicity to vaccine components will be measured by ELISA and indirect bactericidal assays. Sera will be stored and assays will be conducted on batched samples after all sera have been collected.

• Standard ELISA will be performed to determine the level of J8 peptide-specific serum IgG concentrations (µg/ml) in sera of all participants at the time intervals described in Appendix A. Purified human peptide specific antibodies from sera obtained from donors will be used to generate a standard curve, as well as a positive control for each ELISA plate.

• Indirect Bactericidal Assay: This assay will be used to measure the neutralization abilities of the vaccine-induced antibodies against different standard group A streptococcus strains in accordance to the protocol specific SOP. In this assay the percent reduction on GAS colony forming units (CFU) will be determined. As a control a panel of donors will be used to determine the base level of bacterial growth.

• The change in the baseline level of anti-D antibodies in the sera of all participants will be investigated at the end of the study. Anti-D antibodies will be measured by ELISA.

### Specimen Preparation, Handling, and Shipping

#### Instructions for Specimen Preparation, Handling, and Storage

All samples will be collected in accordance to the nominated laboratory procedures and tested in accordance to approved SOP for the specified testing. Collected sera samples will be batched and stored at -20 °C or below until required for testing unless otherwise specified.

Participants will be asked to provide consent for future use of the retained samples in the consent form for research related to group A streptococcus vaccine development. Once this study is completed, samples belonging to participants who do not consent to have their samples to be used in future research will have all labels removed and the samples will be destroyed. Samples from participants who agree for their samples to be used for future research use will remain stored at -80 °C. Before future use of these samples, the project intended for use will undergo ethical and scientific review by the appropriate ethics committee.

# Assessment of Safety

## Specification of Safety Parameters

Adverse events will be monitored starting with the observation period post product administration through the duration of the study.

## Methods and Timing for Assessing, Recording, and Analyzing Safety Parameters

### Adverse Events

The CI is responsible for reporting all AEs that are observed or reported during the study, regardless of their relationship to the study product administered.

According to ICH E6 Good Clinical Practice Guidelines [3], an Adverse Event (AE) is defined as any untoward medical occurrence in a participant regardless of its causal relationship to the study treatment. An AE can therefore be any unfavorable and unintended sign (including an abnormal laboratory finding), symptom, or disease temporally associated with the use of medicinal (investigational) product. Thus, any change from the baseline would be referred as an adverse event.

Unsolicited adverse events will be captured during observation and examination of each participant through the course of the study and recorded using study source documents. All participants will be required to record any observed adverse event regardless of the relationship to the study product in the provided memory aid if it occurs within 7 days after the administration of the study product. Any AE that occurs after the memory aids have been reviewed should be reported to the clinical study personnel during the scheduled interim visits and interviews or by calling the designated contact person.

Each solicited adverse event will be collected from reviewing the memory aids through interview with the participant or on the source document designed to collect solicited reactogenicity. Solicited adverse events will be graded for intensity, according to the criteria in the table below. Solicited adverse events include the following reactions:

• Local reactions:

Redness / erythema

Swelling / induration

Pain at the injection site

Tenderness

Itchiness (pruritus)

• Systemic reactions:

Fever

Malaise (feeling unwell),

Diarrhea

Loss of appetite (anorexia)

Vomiting

Headache

Myalagia (muscle ache)

Joint pain/swelling (arthalgia/arthritis)

Tiredness

Rash

Nausea

Feeling feverish

Chills

Shortness of breath (dyspnoea)

Wheezing

Abdominal pain

The solicited injection site reactions, such as redness/erythema and swelling/induration are to be measured with the provided injection site reaction measurement tool (Appendix C). For the pain at the injection site and the systemic symptoms, the following guidelines will be used to quantify intensity see below and Appendix B:

| **Local reaction to study product** | **Mild**  **(Grade 1)** | **Moderate (Grade 2)** | **Severe**  **(Grade 3)** | **Potentially Life Threatening (Grade 4)** |
| --- | --- | --- | --- | --- |
| Pain | Does not interfere with usual activities | Repeated use of non narcotic pain reliever  > 24 hours or interferes with activity | Any use of narcotic pain reliever or prevents daily activity | Emergency room (ER) visit or hospitalization |
| Tenderness | Mild discomfort to touch | Discomfort with movement | Significant discomfort at rest | ER visit or hospitalization |
| Erythema/  Redness | 2.5 - 5 cm | 5.1 – 10 cm | > 10 cm | Necrosis or exfoliative dermatitis |
| Induration/Swelling | 2.5 - 5 cm and does not interfere with activity | 5.1 – 10 cm or interferes with activity | > 10 cm or prevents daily activity | Necrosis |

| Systemic reaction to injectable product | **Mild**  **(Grade 1)** | **Moderate (Grade 2)** | **Severe**  **(Grade 3)** | **Potentially Life Threatening (Grade 4)** |
| --- | --- | --- | --- | --- |
| Fever (°C)^  (°F) | 38.0 – 38.4  100.4 – 101.1 | 38.5 – 38.9  101.2 – 102.0 | 39.0 – 40  102.1 - 104 | > 40  > 104 |
| Other solicited events | Does not interfere with usual activities | Repeated use of non narcotic pain reliever  > 24 hours or interferes with activity | Any use of non-narcotic pain reliever or prevents daily activity | Emergency room (ER) visit or hospitalization |
| Unsolicited events | Should be graded according to the criteria in Appendix B | | | |

Adverse events characterized as intermittent require documentation of onset and duration of each episode.

All unsolicited AEs must be graded for severity and relationship to study product (see below and Appendix B).

Information collected will include the type of the AE, the onset and the severity of the AE (see table above and appendix B). All changes in the severity of an AE should also be recorded on source documents or medical records to document the duration of the AE at each level of intensity. Adverse events characterized as intermittent require documentation of onset and duration of each episode.

If the CI has any doubt as to whether a clinical observation is an AE, the event will be recorded in the appropriate CRF.

The clinician’s assessment of the relationship of an AE to study product is part of the documentation process, but it is not a factor in determining what is or is not reported in the study. If there is any doubt as to whether a clinical observation is an AE, the event should be reported. All AEs must have their relationship to study product assessed using the following terms: associated or not associated. In a clinical trial, the study product must always be suspect. To help assess, the following guidelines are used:

• Associated – The event is temporally related to the administration of the study product and no other etiology explains the event.

• Not Associated - The event is temporally independent of study product and/or the event appears to be explained by another etiology.

Any medical condition that is present at the time that the participant is screened and found eligible should be recorded and be considered as baseline. However, if it deteriorates at any time during the study, it should be recorded as an AE.

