## Planned Interim Analyses

### Safety Review

Approximately seven weeks after the first product administration, the Safety Monitoring Committee (SMC) will review study data accumulated up to the five-week time point. The SMC is responsible for monitoring participant safety in this QIMR sponsored study. The SMC will review factors that might compromise the study, such as protocol deviations, and losses to follow-up, and the accumulated safety data.

The data presented to the SMC will not be separated by treatment group. Specifically, data from saline and vaccine candidate recipients will be pooled. SMC members may request additional unblinded analyses at their discretion. The SMC will make recommendations to the Chief Investigator and QIMR as to whether the study should continue, be modified, or terminated, and specifically, whether corrective actions are required, or the study may proceed as planned to the second dose of product.

In the SMC report, the demographics of study participants: age, gender, race and ethnicity; will be tabulated. A table of study completion status will display the counts of participants who are in follow-up, have terminated, or have completed the trial by study group. All subjects dropped from the study will be listed, with the date of termination, length of time on study, and reason for termination. Participant specific protocol deviations will be tabulated according to category and reason for deviation.

Reported safety data will include unsolicited adverse event reports, reactogenicity solicited at one-week post-product administration; hematology, chemistry, and urinalysis at four weeks post-product administration. Additionally, analyses will be conducted with ECG, ECHO at four weeks post-product administration and at the final study visit.

Adverse events will be classified and counts will be expressed in terms of the number and percentage of participants experiencing the event.

Local and systemic reactogenicity will be classified by reaction type, and the maximum grade over the follow-up period for each participant will be reported. The frequency of occurrence and severity of reactogenicity assessments will be summarized in tables and bar-charts.

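### Section 9.2.1 ends its adverse event definition by counting any change from baseline, which conflicts with the rest of the section and leaves unsolicited, laboratory and examination-based AE counts without one clear rule

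*Protocol*

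**What the plan says.** Section 9.2.1 (Adverse Events) takes the ICH E6 definition as its base: "any untoward medical occurrence in a participant regardless of its causal relationship to the study treatment". It explains this as follows: "An AE can therefore be any unfavorable and unintended sign (including an abnormal laboratory finding), symptom, or disease". The paragraph then closes with "Thus, any change from the baseline would be referred as an adverse event".

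Other current text bears on the same question:

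- **Later in 9.2.1**, a condition present at screening is treated as baseline. The section adds: "However, if it deteriorates at any time during the study, it should be recorded as an AE".
- **Also in 9.2.1**, every unsolicited AE must be graded for severity and judged associated or not associated. On borderline cases: "If there is any doubt as to whether a clinical observation is an AE, the event should be reported".
- **Section 9.2.3** says that the Appendix B toxicity tables grade a laboratory abnormality.
- **Section 9.4** has all AEs followed until resolved or stabilized. **Section 9.3.2** puts AEs that need no expedited report into at least annual summaries for the ethics committees and the TGA.
- **Section 11.9.1**, on the Safety Monitoring Committee (SMC) report: "Adverse events will be classified and counts will be expressed in terms of the number and percentage of participants experiencing the event".

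**The concern.** The closing sentence is a data-capture rule, and it is wider than the definition it claims to summarise. It has no direction, no size and no abnormality requirement. An improvement counts, and so does a sodium value that moves by one unit inside the normal range.

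At stake is whether AE counts mean the same thing from one assessor to the next. Someone who follows the closing sentence records far more events than someone who follows the ICH wording or the deterioration rule, and the instruction to report when in doubt favours the wider reading. With 15 vaccine and 5 saline participants, one differently classified participant moves an arm's percentage by 1/15 = 6.7 or 1/5 = 20 points. A later analysis plan cannot repair this, because it would receive events already recorded under different rules.

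**Working it through.** **1. The rules side by side**

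| Case | ICH wording (9.2.1) | Deterioration rule (9.2.1) or graded abnormality (9.2.3) | Closing sentence (9.2.1) |
|---|---|---|---|
| Baseline condition improves | not an AE | not an AE | AE |
| Laboratory value shifts within the normal range | not an AE | no abnormality to grade | AE |
| Out-of-range value, not clinically significant at entry (allowed by 7.1), returns to normal | not an AE | no abnormality remains | AE |
| Baseline condition worsens | AE | AE | AE |

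The rules agree only on worsening. In the first three rows the closing sentence creates an event that must be graded although it has no severity.

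**2. Size of the effect if the sentence is followed**

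The protocol states no AE rate, so there is no figure to reproduce.

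*Inputs from the documents*

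- Analytes (8.2.1): 11 numeric biochemistry values, counting creatinine once although it is listed twice, plus 6 haematology values (Hb, RBC, Hct, MCV, platelets, total WBC). Total k = 17. The differential, vital signs and screening-only tests are left out.
- Visits (Section 4): Days 28, 56 (pre-dose), 84, 180, 266 and 350, so v = 6.
- Results per participant: 17 × 6 = 102.

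*Assumptions*

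- The full list is run at each visit. Appendix D, which assigns tests to visits, is not shown, so the biochemistry panel alone (k = 11) is given as a lower case.
- q is the chance that one result counts as an event.
- Results are independent. Positive correlation lowers the figures. The v = 1 columns show the extreme where later visits add nothing.

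*Formula:* P(at least one event) = 1 − (1 − q)^(k·v)

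| q (assumed) | k=11, v=1 | k=11, v=6 | k=17, v=1 | k=17, v=6 |
|---|---|---|---|---|
| 0.50 (any change) | 0.9995 | 1.000 | 1.000 | 1.000 |
| 0.20 (any change, cautious) | 0.914 | 1.000 | 0.977 | 1.000 |
| 0.05 (outside a 95% reference range) | 0.431 | 0.966 | 0.582 | 0.995 |
| 0.01 (rarer, clinically relevant) | 0.105 | 0.485 | 0.157 | 0.641 |

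Under the literal rule (first two rows) the expected picture with no vaccine effect is about 15/15 and 5/5.

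Counting by type of event does not remove the problem. For a single analyte with q = 0.20, the chance of at least one change over six visits is 1 − 0.8^6 = 0.738.

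**3. What the table says about the fix**

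At q = 0.05 and 102 results, 1 − 0.95^102 = 0.995. Requiring only that a value be outside the reference range would therefore still make nearly everyone a case. At q = 0.01 the figure is 1 − 0.99^102 = 0.641. A grade or clinical-significance threshold is what makes the difference.

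**The case against.** The best reply is that the sentence opens with a word of inference and follows the ICH text directly, so the change it means is an untoward one. The deterioration rule, the grading of abnormalities in 9.2.3 and the grading of examination deviations in 8.1 all fit that reading. This stands in part: the sentence is one of two conflicting rules, not the only one in force. It does not remove the conflict, because the sentence is current text and the when-in-doubt instruction leans towards it.

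A reader might go further and infer that the sentence disables a primary endpoint, so that the trial cannot tell vaccine from saline on safety. The documents do not support that:

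- Sections 3.2.1 and 11.2.1 base safety on injection site and systemic reactions, with AEs and SAEs reported alongside. The list of primary safety assessments in 11.5 has no unsolicited-AE frequency, and no overall any-AE percentage is specified anywhere.
- Section 11.9.1 counts participants by classified event and pools the arms by default, so a 15/15 against 5/5 display is not planned for the SMC.
- SAEs, the solicited reactions graded in 9.2.1 and the numeric halting criteria in 9.5 have their own definitions.
- Sections 11.6 and 11.7 plan descriptive statistics and disclaim power. Even with a clean definition, two-sided Fisher power at 15 against 5 is only about 24% for 60% vs 20% and 35% for 90% vs 50% (rates and 5% level assumed).

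These points limit the reach of the problem. A descriptive count still needs a definition.

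**Conclusion.** The sentence is wrong as written. It does not follow from its own paragraph, and it conflicts with the deterioration rule in 9.2.1 and the abnormality grading in 9.2.3. Followed literally, it makes almost every participant in both arms an AE case regardless of vaccine effect. That result needs only the assumption that a participant's results seldom all match baseline; the particular q values and independence are illustrative.

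The damage is limited to unsolicited, laboratory and examination-based AE counts and listings, and to the grading, association and follow-up work that goes with them. It is a real inconsistency, worth correcting at small cost, and not a failure of the primary safety assessment.

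**What to change.** In Section 9.2.1, delete the sentence or replace it with wording such as: *any new or worsened unfavorable and unintended change from baseline, including a laboratory, vital-sign, ECG or ECHO result that newly reaches or worsens in an Appendix B grade or is judged clinically significant by the CI*. Use this one definition for the AE counts in 11.9.1 and in the final analysis.

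Appendix B is not shown. Its lowest grade decides how far the counts fall, so its thresholds must be checked when the wording is adopted.

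The cost is one sentence in an amendment and matching CRF guidance, with no extra visits, samples or participants. The small downside is that sub-threshold changes leave the AE listings. Laboratory and vital-sign changes remain visible in the summaries and scatter plots already planned in 11.9.1.

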## Concomitant Medications/Treatments

Concomitant medications/treatments will be recorded during the 0-7 days following each dose and at the scheduled study visits (see Appendix A) and collected surrounding adverse events/serious adverse events. This documentation will include any prescription or nonprescription drug or other treatment. The name of the medication, start and stop dates of treatment, total daily dose, route of administration and indication will be recorded on the source documents.

Permitted concomitant medications:

- These medications include licensed hormonal contraceptives, antihistamines and decongestants for seasonal allergies, non-steroidal anti-inflammatory drugs, (e.g., ibuprofen), non-narcotic analgesics (e.g., paracetamol/acetaminophen) and antibiotics as medically indicated.

At each of the scheduled visits circumstances that could potentially interfere with the vaccine-induced immunity will also be checked for. These circumstances include:

1. Use of any investigational drug or investigational vaccine other than the study vaccine during the study period.

2. Administration of licensed vaccines within 30 days prior to screening and enrollment through to 30 days following the last study vaccine administration, with the exception of licensed inactivated influenza vaccines.

3. Administration of immunosuppressants or other immune-modifying drugs (as listed in the exclusion criteria)

4. Administration of immunoglobulins and/or any blood products up to 28 days after the last dose of vaccine.

5. Antibiotics prescribed for streptococcal throat infection.

If any of the participants require medications/treatments that are listed as exclusion criteria, the participant will be excluded from receiving further doses of the vaccine and will not be included in the immunogenicity evaluations. However, the participant will be encouraged to continue the scheduled follow-up visits and remain in the study for safety evaluation for doses already received.

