### Adverse Event Severity – Definition

The severity of adverse events will be graded on a three point scale:

**Mild**: discomfort noted, but no disruption to normal daily activities.

**Moderate**: discomfort sufficient to reduce or affect normal daily activities.

**Severe**: inability to work or perform normal daily activities.

**Potentially Life Threatening:** participant at immediate risk of death

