## Halting Rules

Study product administration in the trial will be halted for expedited ISM/SMC review if, during the 7 days after product administration, any of the following occur:

• One (1) or more participants experiences an SAE that is unexpected and associated with study product administration

• 10% or more of the participants enrolled to date experience a severe (grade 3) study product associated fever

• 10% or more of the participants enrolled to date experience a severe (grade 3) study product associated local redness or induration;

• 10% or more of the participants enrolled to date experience a severe (grade 3) study product associated subjective reaction (pain, headache, malaise or myalgia), the severity of which is corroborated by study personnel

• One (1) or more participants experience a study product -associated bronchospasm or other anaphylactic response

• One (1) or more participants experience a study product-associated allergic event or vaccine site ulceration, abscesses or necrosis

The trial will be halted at any time if there is:

• Any patterns of laboratory values or clinical symptoms that the CI considers to be a significant safety issue for participants or any clinical symptoms of rheumatic carditis and/or rheumatic fever as defined by Jones criteria. (see Appendix G).

• ECG or ECHO abnormality such as:

- Increase in valvular regurgitation to greater than mild severity;
- Development of mitral regurgitation with an EROA of 20mm2 or >10mm2 increase from the baseline study;
- An absolute increase in effective regurgitant area of 10mm2 compared to baseline;
- Development of mitral regurgitation with an EROA > 20 mm2 and

echocardiographic criteria of probable RHD will require notification of the appropriate regulatory bodies as associated SAE.

- Any abnormal valve leaflet thickening (subjective);
- Worsening left ventricular systolic function (ejection fraction of < 50%);
- Left ventricular dilatation (based on LV diameter > upper limit of reference ranges for LV end diastolic diameter (LVEDd) indexed for body surface area (Females 24-32 mm/sqm; Males 22-31mm/sqm);
- Significant right ventricular dysfunction;
- Evidence of pulmonary hypertension (estimated RVSP > 40mmHg);
- Development of more than trivial pericardial effusion;

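### Grade 3 for solicited systemic reactions other than fever covers any non-narcotic analgesic use, which swallows the Grade 2 criterion, contradicts the Pain row and feeds a halting rule

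*Protocol*

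**What the plan says.** Section 9.2.1 (Adverse Events) makes its tables the grading instrument: "Solicited adverse events will be graded for intensity, according to the criteria in the table below". In the systemic table, one row covers every solicited event except fever, and so includes headache, malaise and myalgia. Its Grade 2 cell begins "Repeated use of non narcotic pain reliever", qualified as more than 24 hours, with interference with activity as the alternative. Its Grade 3 cell reads "Any use of non-narcotic pain reliever or prevents daily activity".

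The Pain row of the local table in the same section has the same Grade 1, Grade 2 and Grade 4 text, but its Grade 3 cell reads "Any use of narcotic pain reliever or prevents daily activity". The later heading, Adverse Event Severity – Definition, describes severe as "inability to work or perform normal daily activities" and has no analgesic criterion.

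Three other places bear on the consequence:
- Section 6.4 lists "non-narcotic analgesics (e.g., paracetamol/acetaminophen) and antibiotics as medically indicated" among permitted medications and has concomitant medications recorded over days 0 to 7 after each dose.
- Section 11.9.1 (Safety Review) reports each participant's maximum grade for each reaction type and summarises severity in tables and bar charts.
- Section 9.5 (Halting Rules) halts dosing for expedited review if, within 7 days of a dose, "10% or more of the participants enrolled to date experience a severe (grade 3) study product associated subjective reaction". The reactions named are pain, headache, malaise and myalgia, and study personnel must corroborate the severity.

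**The concern.** A severity scale has to be ordered, and each event should fall into one grade. This row fails on both counts. The lighter condition (any use) sits above the heavier one (repeated use beyond 24 hours), and a participant who takes one tablet and carries on as usual satisfies the lowest grade and the severe grade together.

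Two things are at stake. The severity profile of systemic reactions goes to the Safety Monitoring Committee before Dose 2, by default pooled over arms, and it could show self-treated mild events as severe. The same grade also drives a halting rule whose threshold is very few people in a trial of 20. The input that sets off the problem, use of a permitted over-the-counter analgesic, is something the protocol systematically records.

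**Working it through.** **Logic of the row.** Let A be any non-narcotic use and R be repeated non-narcotic use for more than 24 hours. R is contained in A. Grade 2 (by analgesic) requires R and Grade 3 (by analgesic) requires A, so everyone who meets R also meets Grade 3. Under maximum-grade reporting, the Grade 2 analgesic criterion never sets the result. A person in A whose activity is unaffected meets Grade 1 and Grade 3 at once.

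**The texts side by side.**

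| Source in the Protocol | Grade 2 or moderate | Grade 3 or severe |
|---|---|---|
| 9.2.1, systemic row | repeated non-narcotic use > 24 h, or interferes with activity | any non-narcotic use, or prevents activity |
| 9.2.1, local Pain row | same as above | any narcotic use, or prevents activity |
| Adverse Event Severity – Definition | reduces or affects normal activities | unable to work or carry out normal activities |

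The two Grade 3 cells in the tables differ only in whether the analgesic is narcotic. The cell is a complete phrase, so broken table extraction does not explain it.

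**Halting threshold.** The protocol states 10% of those enrolled to date. With 20 enrolled, 0.10 × 20 = 2 participants. While only the two sentinels are enrolled, 0.10 × 2 = 0.2, so a single event (1 of 2) meets it.

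**How easily two events could arise.** The documents give no rate of associated headache, malaise or myalgia treated with a non-narcotic analgesic, so the rate p is an assumption. I take the 15 vaccinees (section 11.7) as independent, let only them contribute, and suppose that every such event is judged associated, graded literally and corroborated. Per dose:

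P(at least 2) = 1 − (1 − p)^15 − 15p(1 − p)^14

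| Assumed p | (1 − p)^15 | 15p(1 − p)^14 | P(at least 2 of 15) |
|---|---|---|---|
| 5% | 0.463 | 0.366 | 0.171 |
| 10% | 0.206 | 0.343 | 0.451 |
| 20% | 0.035 | 0.132 | 0.833 |
| 30% | 0.005 | 0.031 | 0.965 |

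If saline recipients contributed at the same rate (n = 20), the values would be 0.264, 0.608, 0.931 and 0.992. For contrast, if qualifying events were rare, at an assumed 1% or 2% of the 15 vaccinees, the chance would be 0.010 or 0.035.

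The protocol states no power or alpha that depends on this point, so there is no planned figure to reproduce.

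**The case against.** The case for leaving the text alone has several parts.

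- **Judgment.** Section 4 lets staff use clinical judgment on severity, section 9.2.1 calls the criteria for pain and systemic symptoms guidelines and also points to Appendix B, and section 9.5 requires both product association and corroborated severity. A sensible assessor may never grade one tablet as severe. This can reduce false triggers but does not cure the defect. Staff who follow the table would confirm Grade 3, and staff who override it would depart from the written criteria, so grading would depend on the assessor. Appendix B is not in the text at hand. Even if it is sound, section 9.2.1 cites both sources and the conflict would remain.
- **Primary outcome.** A reader might infer that the primary safety outcome is corrupted. The documents do not support that. Section 3.2.1 rests on the frequency and occurrence of reactions, and misgrading changes neither. Fever, redness, induration, tenderness and injection-site pain have rows of their own. The study is descriptive, so no test is affected.
- **Halting.** A reader might take the probabilities above as the trial's expected chance of stopping. They are not. The rates are assumed, every event is taken as associated and corroborated, and a trigger under this rule pauses dosing for expedited review without terminating the study. The error also leans towards caution: it adds reviews and does not hide severe events.
- **The correct word.** It is tempting to say that the Pain row shows what was meant. The similarity is suggestive, but the documents do not settle which criterion applies, and the choice feeds a rule that stops dosing.

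The limits on occurrence, on the meaning of the probabilities and on prescribing a criterion all stand. The inversion itself is not answered.

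**Conclusion.** The point holds as an internal contradiction in an outcome definition, and it should be fixed before dosing. The systemic row is unordered on its face and disagrees with the Pain row and with the general definition of severe.

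Its reach is limited to the severity distribution of solicited systemic reactions other than fever and to the headache, malaise and myalgia parts of one halting rule. That rule is met by 2 of 20 participants, or 1 of 2 at the sentinel stage. The chance of reaching 2 per dose runs from 0.17 to 0.965 as the assumed event rate among the 15 vaccinees runs from 5% to 30%. These values are conditional on independence and on literal grading, association and corroboration of every event. They show that the wording could matter and do not forecast what the trial will do.

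**What to change.** Before Dose 1, reconcile the systemic Grade 3 cell in section 9.2.1 with its own Grade 2 cell, the local Pain row, the Adverse Event Severity – Definition text, Appendix B and the Reactogenicity Record, so that the grades are mutually exclusive and increasing. Then confirm that section 9.5 refers to the reconciled Grade 3. The sponsor and investigator decide which criterion is right.

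The cost is a small edit to the table and a check of the grading documents and data-collection form. There is one downside to weigh: if the reconciled Grade 3 is narrower than the present wording, the halting rule will trigger less readily than the literal text implies, so the change should be made knowingly and not treated as purely editorial.
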